### Follow-up

The follow-up assessment, which is designed to evaluate the clinical curative effect and long-term effects of acupuncture, as well as safety of the study, will be carried out 2 weeks after the end of treatment. Patients will document the details of clinical symptoms and adverse events, and send the relevant information to researchers via call, email, or short message service.

### Statistical analysis

In this study, statistical analysis will be performed by a professional statistician blinded to the whole trial process using SPSS19.0 statistical software, and based on the intention-to-treat principal and preprotocol population. All demographic, baseline characteristics, curative effects, and fMRI images of the subjects will be analyzed with different approaches.

In terms of the data description, the enumeration data/quantitative data will be expressed with/as a percentage or proportion, while the measurement data/qualitative data will be represented as average and standard deviation. On this occasion of normal distribution and homoscedasticity, one-way analysis of variance (ANOVA) will be applied to identify differences in measurement data/qualitative data of comparison. Other covariates will be considered for further revision and if necessary stated in the statistical analysis project prior to data lock. Similar analysis of covariance (ANCOVA) models will used for secondary analysis to adjust baseline characteristics. A *q* test (Newman–Keuls) will be used for pairwise comparison. In case of nonnormally distributed data and heteroscedasticity data, a nonparametric test (Kruskal–Wallis *H* test) will be performed, and a rank sum test (Nemenyi) will be conducted to identify difference between groups. The enumeration data/quantitative data will be compared by chi-square test, while classification data will be evaluated with a rank sum test. In addition, the exploratory analysis will be implemented to describe group means over time. A two-sided test will be applied for available data and *p* < 0.05 will be taken as significant for each outcome. Missing data will be explored and if necessary multiple imputations will be utilized.

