#### Outcome assessments/measurement

All of the outcomes will be assessed twice before and after the intervention treatment.

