### Primary outcome

#### Pittsburgh Sleep Quality Index

The Pittsburgh Sleep Quality Index (PSQI), a self-rated questionnaire that evaluates sleep quality and disturbance over 1 month [20], is applied as the primary outcome measurement for clinical effectiveness assessment. The constructive validity and reliability of the PSQI to measure changes of sleep quality have been confirmed in previous studies all over the world. It is widely used to measure response to treatment in research studies and clinical trials. The PSQI is comprised of 19 items which consist of the following seven component scores: subjective sleep quality, sleep latency, sleep duration, sleep efficiency, sleep disturbance, use of hypnotic medication, and daytime dysfunction. Each item is weighted equally on a 4-point scale, from 0 to 3, with 0 indicating no dysfunction and 3 indicating the worst dysfunction. The seven component scores are then added to provide a global PSQI score. In general, a lower global score reflects a better sleep quality [21].

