
Nevertheless, there are also limitations in this study. Concerning the unfeasible blinding to participants, one limitation is the possibility of a high risk of bias regarding blinding by unconcealed allocation. We therefore strictly conduct randomization and separate the acupuncturist, assessor, and statistician. Meanwhile, patients divided into the acupuncture intervention group may have more opportunities to make contact with their acupuncturists and establish a good doctor–patient relationship rather than those of the western medicine control group, which is likely to improve the therapeutic effect [57]. Hence, we will maintain close contact with patients in the control group by telephone, Internet, and so on, to minimize this potential bias.

In conclusion, the results of this trial are expected to confirm whether an acupuncture formula based on liver differentiation is effective in relieving perimenopausal insomnia. Combining neuroimaging with a neurophysiology method, the relevant outcomes are predicted to verify the central mechanism of acupuncture treatment. We believe that the results will exert a positive effect on acupuncture treatment for perimenopausal insomnia (Additional files 1 and 2).

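### The main PSQI comparison is an unadjusted ANOVA, with baseline-adjusted ANCOVA only secondary; making ANCOVA primary would gain precision from data already collected

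*Protocol article*

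**What the plan says.** The protocol article, under Statistical analysis, fixes the lead test for continuous outcomes when normality and equal variance hold: "one-way analysis of variance (ANOVA) will be applied to identify differences in measurement data/qualitative data of comparison". When they fail, "a nonparametric test (Kruskal–Wallis *H* test) will be performed". Neither uses a covariate. Baseline adjustment comes later and lower: "Similar analysis of covariance (ANCOVA) models will used for secondary analysis to adjust baseline characteristics". Further covariates are deferred: "Other covariates will be considered for further revision and if necessary stated in the statistical analysis project prior to data lock".

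The PSQI "is applied as the primary outcome measurement for clinical effectiveness assessment". Its baseline value will be available, since "All of the outcomes will be assessed twice before and after the intervention treatment".

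The Setting and Randomization sections describe 1:1 allocation from a random number table and mention no stratification. The Sample size section plans 20 patients per group on the basis of an fMRI rule of thumb, with no PSQI effect size, standard deviation or power.

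**The concern.** The pre-treatment score is usually among the best predictors of the post-treatment score on the same scale. Here it is collected in every patient, but the main comparison does not adjust for it.

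With 20 per arm and simple randomisation, the arms can start visibly apart on PSQI by chance. An unadjusted comparison of post-treatment scores carries part of that gap into the treatment estimate. A comparison of change scores over-corrects for it, because patients who start worse tend to regress. Both have a larger variance than the adjusted model. Since the sample size was not set for PSQI, precision on the primary outcome was never planned for and should not be given away.

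**Working it through.** **Inputs from the protocol article.** n = 20 per arm (Sample size); simple 1:1 allocation (Setting, Randomization); two-sided 0.05 (Statistical analysis); one PSQI score before and one after treatment (Outcome assessments/measurement).

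**Assumptions.** The pre-post correlation ρ is not in the documents, so 0.3, 0.5 and 0.7 are shown. The PSQI standard deviation is taken as equal before and after treatment, and results are in units of that SD. The planned N of 40 cannot be reproduced, because no effect size, SD, power or dropout figure is given.

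**Step 1: chance imbalance.** SD of the baseline mean difference = √(2/20) = 0.316 SD, so the 95% range is ±1.96 × 0.316 = ±0.62 SD. P(|difference| > 0.25 SD) = 43%; P(|difference| > 0.5 SD) = 11.4%.

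**Step 2: variance of the treatment effect.** Relative to post-score ANOVA = 1, change-score ANOVA has 2(1 − ρ) and ANCOVA has 1 − ρ². The ratio of ANCOVA to change score is (1 − ρ²)/[2(1 − ρ)] = (1 + ρ)/2. Equivalent N is 40 divided by the relevant ratio.

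| ρ | ANCOVA / post score | Cut | Equivalent N | ANCOVA / change score | Cut | Equivalent N |
|---|---|---|---|---|---|---|
| 0.3 | 0.91 | 9% | 44 | 0.65 | 35% | 62 |
| 0.5 | 0.75 | 25% | 53 | 0.75 | 25% | 53 |
| 0.7 | 0.51 | 49% | 78 | 0.85 | 15% | 47 |

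These ratios treat the baseline slope as known. Estimating it inflates the ANCOVA variance by an expected factor of 1 + 1/(40 − 4) = 1.028, which lowers each equivalent N by just under 3% and leaves the picture unchanged.

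**Step 3: detectable difference and power (noncentral t).** At 80% power, post-score ANOVA detects 0.909 SD. Multiplying by √(1 − ρ²) gives 0.87, 0.79 and 0.65 SD for ANCOVA. Power at an assumed true difference of 0.8 SD:

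| ρ | ANOVA, post score | ANOVA, change score | ANCOVA |
|---|---|---|---|
| 0.3 | 69% | 55% | 73% |
| 0.5 | 69% | 69% | 81% |
| 0.7 | 69% | 89% | 93% |

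**Step 4: bias given a 0.5 SD imbalance.** Post-score ANOVA is off by ρ × 0.5 = 0.15, 0.25 and 0.35 SD, and its type I error conditional on that imbalance is 6.5%, 8.9% and 11.6%. Change-score ANOVA is off in the opposite direction by (1 − ρ) × 0.5 = 0.35, 0.25 and 0.15 SD. Under a linear model with a common slope, ANCOVA removes this bias.

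**The case against.** The strongest defence is that this is a choice about efficiency, not an error. Over all randomisations the unadjusted comparison is unbiased and keeps its 5% type I error. ANCOVA is planned, and covariates are to be settled before data lock in a document not shown. At ρ = 0.3, against post scores, the gain is only 0.04 SD in the detectable difference (0.909 against 0.87). All of this stands, and it limits the claim to lost precision and conditional bias. It does not remove the point: the article itself names an unadjusted lead test and ranks the adjusted model second. If secondary analysis is read as analysis of secondary outcomes, the primary PSQI comparison is still unadjusted.

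A reader might infer more than the text supports:

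- **That baseline PSQI is discarded.** The text never names the dependent variable. If it is the change score, baseline is used with a fixed slope of 1, and the equivalent N is 62, 53 and 47 rather than 44, 53 and 78.
- **That a non-significant difference from estazolam will be read as equal effect.** The Discussion says the results are "expected to confirm whether an acupuncture formula based on liver differentiation is effective in relieving perimenopausal insomnia", which leaves the question open. No section claims equivalence or non-inferiority, so the absence of a margin is not a fault here.
- **That the Newman–Keuls and Nemenyi steps distort the result.** With two arms there is only one pair, so they are redundant but do no harm.
- **That the wrong tests are assigned.** In "The enumeration data/quantitative data will be compared by chi-square test" the second label is reversed, as it is for measurement data. Counts still get percentages and chi-square, and measurements still get means and standard deviations. This is copy-editing.

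**Conclusion.** The point holds as a recommended improvement to a stated choice. The main PSQI test is unadjusted although the baseline score is available in everyone. The test is valid on average, but ANCOVA has the smaller variance under either reading of the outcome: by 9% to 49% against post scores and by 15% to 35% against change scores, for ρ from 0.3 to 0.7. About one trial in nine of this size would have a baseline gap above 0.5 SD, and either form of ANOVA would then be off by 0.15 to 0.35 SD. The size of the gain rests on the assumed ρ and on equal SDs before and after treatment. Which comparison applies depends on the outcome score, which the article should name.

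**What to change.** State the primary analysis as ANCOVA of post-treatment PSQI on arm and baseline PSQI in all randomised patients, reported as an adjusted mean difference with 95% CI. Use the same model, each with its own baseline, for HAMD, HAMA and the sleep-monitoring parameters. Keep the unadjusted ANOVA as a sensitivity analysis and say which score it uses. As copy-editing, delete the Newman–Keuls and Nemenyi steps and correct the data-type labels.

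The cost is one degree of freedom and some wording; no extra patients, visits or measurements are needed. The article reports that recruitment is under way and foresees settling covariates before data lock, so the change can still be pre-specified.

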### Sample size

There is so far still no definite sample size calculation for fMRI research; however, as a result of previous fMRI studies, there should be at least 10 participants in each group to obtain brain imaging with statistical significance [18]. Combining the preceding clinical trial experiences all over the world recently with the withdrawal rate, we plan to enroll a total of 40 participants with 20 patients in each group.

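### The trial data choose the main test for PSQI and the other scales, by an ambiguous trigger, and the fallback rank test does not correct for unequal variances; neither branch adjusts for baseline

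*Protocol article*

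**What the plan says.** The Statistical analysis section of the protocol article sets a two-branch rule for continuous outcomes.

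- **First branch:** "On this occasion of normal distribution and homoscedasticity, one-way analysis of variance (ANOVA) will be applied to identify differences". With two arms this is the equal-variance t test, without a covariate.
- **Second branch:** "In case of nonnormally distributed data and heteroscedasticity data, a nonparametric test" is used, named as Kruskal-Wallis and followed by Nemenyi comparisons. With two arms this is the Wilcoxon rank-sum test.
- **Baseline adjustment:** "Similar analysis of covariance (ANCOVA) models will used for secondary analysis to adjust baseline characteristics". Further covariates stay open: "Other covariates will be considered for further revision and if necessary stated in the statistical analysis project prior to data lock".
- **Level:** two-sided, and p < 0.05 "will be taken as significant for each outcome".

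No pre-test or threshold is named for moving between branches, and PSQI is not treated separately. The Sample size section gives the scale: "we plan to enroll a total of 40 participants with 20 patients in each group".

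**The concern.** There are four weaknesses, all in text that the article itself fixes.

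1. **The test is chosen from the outcome data.** Whether PSQI is analysed by means or by ranks is unknown until the data are examined.
2. **The trigger can be read in two ways.** The second branch joins non-normality and unequal variance with an *and*. It may mean that either failure suffices, or that both are needed.
3. **The remedy does not fit the problem.** As a test of location, Kruskal-Wallis needs distributions of similar shape. The plan sends data to it when spread differs, which is when that condition fails.
4. **The main test ignores baseline.** PSQI, HAMD and HAMA are all measured before treatment, yet ANCOVA is only secondary, and the rank branch has no stated adjusted counterpart.

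At stake are a clear primary estimand, an effect estimate with a confidence interval, and power in a trial of 40. Unequal shape is plausible. One PSQI component scores hypnotic use, and every control patient is prescribed estazolam, so that component may cluster in one arm and vary in the other.

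**Working it through.** **Inputs from the article:** two arms of 20, two-sided 0.05, ANOVA or Kruskal-Wallis according to normality and equal variance. The article gives no effect size, SD or power, so there is no planned figure to reproduce.

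**Assumptions, none stated in the article:** Shapiro-Wilk in each arm and Levene's test, both at 0.05; the SD ratios, skewed shapes and unequal arm sizes; a PSQI SD of 3; the baseline correlations.

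**Statistic:** H = 12/[N(N+1)] × Σ(Rj²/nj) − 3(N+1), referred to χ² with 1 df.

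**Step 1. Normal data, equal means, 20:20, switch if either assumption fails.** There were 40,000 runs for the single tests and 8,000 for the rule. The simulation error of the rule is about √(0.05 × 0.95/8000) = 0.24 points.

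| SD ratio | ANOVA | Welch | Kruskal-Wallis | Rule | Sent to ranks |
|---|---|---|---|---|---|
| 1 | 5.1% | 5.0% | 5.0% | 5.4% | 15% |
| 1.5 | 5.2% | 5.1% | 5.3% | 5.5% | 42% |
| 2 | 5.1% | 4.8% | 5.6% | 5.3% | 79% |
| 3 | 5.5% | 5.1% | 6.7% | 7.1% | 99% |

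With equal arms, Kruskal-Wallis is further from 5% than ANOVA once variances differ, so it does not repair the problem. The excess is small.

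**Step 2. The trigger.** For normal data at SD ratio 2, the switch occurs in about 75% of trials if either failure suffices (median-centred Levene) and in about 5% if both are needed. Two statisticians following this text would often run different primary tests.

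**Step 3. Skewness together with unequal spread, equal means, 20:20.** A gamma variable with mean 1 and shape k has SD 1/√k. Shapes 1.5 and 6 give SDs 0.816 and 0.408, and shapes 2 and 8 give 0.707 and 0.354, a ratio of 2 in both cases.

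- Switch if either fails: 13.0% and 11.2% (Welch 5.9% and 6.0%).
- Switch only if both fail: 5.8% and 6.2%. A check with 20,000 runs gave 6.2% and 6.0% with median-centred Levene, but 8.6% and 7.6% with mean-centred Levene.
- A harsher case, centred exponentials with SD ratio 2 and 3 and the either-fails trigger: 19.0% and 26.4% (ANOVA 6.1% and 7.6%, Welch 5.9% and 7.3%). With the both-fail trigger at ratio 3, the same check gave 14.8% (median-centred) or 21.7% (mean-centred).

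The reason is that equal means do not imply equal ranks. Let X = E₁ − 1 and Y = 2(E₂ − 1), with E₁ and E₂ standard exponentials. Both means are 0, but P(X < Y) = (2/3)e^(−1/2) = 0.404, not 0.5. The rank test correctly detects that difference, but it is not a difference in means.

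**Step 4. Unequal arms (24:16, smaller arm more variable, normal data).** At SD ratios 2 and 3, repeated runs gave 7.7% to 8.6% and 8.7% to 9.7% for the rule, and 8.6% to 9.4% and 9.6% to 9.9% for plain ANOVA. Welch gave 4.9% and 5.2%.

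**Step 5. Power for a PSQI difference of 2.7 (2.7/3 = 0.9 SD), 20 per arm.**

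- Rule 77.9%, plain ANOVA 78.3%, Welch 78.1%. The switch costs 78.3 − 77.9 = 0.4 points.
- ANCOVA with HC3 standard errors: about 80%, 86% and 91% at baseline correlation ρ = 0.3, 0.5 and 0.6.

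The normal approximation agrees in direction. ANCOVA reduces the residual SD by √(1 − ρ²). At a difference of 0.8 SD, unadjusted power is Φ(0.8/√(2/20) − 1.96) = Φ(0.57) = 0.72. With ρ = 0.5 it is Φ(0.8/(0.866 × √(2/20)) − 1.96) = Φ(0.96) = 0.83.

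**The case against.** The strongest defence is that the harm is small in the design as planned. With 20 per arm and roughly normal scores the rule stays near its level, and a threefold SD ratio on a bounded score is not supported by anything in the article. If the treatments do not differ at all, randomised arms share one distribution and the rule holds its level: simulation gave 4.6% for PSQI-like scores and 5.3% for strongly skewed ones. The excess rejections in step 3 concern a narrower null, in which means agree but distributions differ. All of this stands, and it rules out saying that the p-value has no meaning.

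A reader might infer three stronger points that the documents do not support:

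- **That the switch discards the baseline adjustment.** The main ANOVA is already unadjusted and ANCOVA is assigned to secondary analysis, so the switch removes nothing from the main test. Nor does the text say that the secondary ANCOVA is dropped when ranks are used.
- **That the switch causes the error at 24:16.** Plain ANOVA shares it. It comes from unequal arms combined with unequal variances.
- **That the switch costs material power.** It costs about 0.4 points. The larger gap is the value of the baseline covariate.

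It may also be said that an unseen analysis plan could settle the details. It could name pre-tests and covariates, but the switch and the choice of a rank test for unequal variances are already fixed in the article. Finally, Welch's test is not exact everywhere: it reached 7.3% in the harshest skewed case.

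**Conclusion.** The point holds and should be corrected, but it does not invalidate the trial. The main test for PSQI depends on the observed data through a trigger with two readings. Its fallback does not correct for unequal variances and changes the effect being tested, and neither branch uses the baseline score.

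Under the assumed pre-tests, type I error for equal means at 20:20 is about 5% to 7% with normal data and SD ratios up to 3. It is about 10% to 14% in the gamma examples, which need skewness and unequal spread together and a switch on one failed assumption. With the both-fail reading it falls to about 6% to 9% there, depending on the form of Levene's test. The exponential case shows that stronger skewness can give more under either reading. These sizes rest on assumed shapes and pre-tests. The ambiguity and the mismatched remedy follow from the text alone.

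**What to change.** Remove the distribution-based switch. State one primary analysis of post-treatment PSQI: ANCOVA with treatment arm and baseline PSQI, heteroscedasticity-robust (HC3) standard errors, reporting the adjusted mean difference with its 95% confidence interval. Use the same model for HAMD and HAMA. Use Welch's test for any continuous outcome without a baseline value. Keep the rank test as a labelled sensitivity analysis whatever the data look like. Make the change before any outcome data are examined by arm.

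**Cost:** wording only, since baseline PSQI, HAMD and HAMA are already collected. For heavy-tailed outcomes the model has slightly less power than a rank test. HC3 costs roughly one to two percentage points of power at this sample size, which the baseline covariate more than repays if the correlation is about 0.5 or higher. At 0.3 the net gain is small.

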### Safety monitoring

To exclude patients who have severe heart, liver, and kidney diseases, all participants will receive routine tests of blood, urine and stool, liver function, kidney function, and electrocardiogram before randomization. Meanwhile, aiming to evaluate the side effects of both interventions, participants will receive these examination items again after the end of treatment.

Possible adverse events due to acupuncture include needle fainting, needle sticking, local infections, subcutaneous hematoma, and so forth. Any adverse events or reactions occur during the study process will be addressed properly and analyzed by the investigator. Serious adverse events associated with the trial should be reported to the principal investigator immediately. All unexpected and unintended responses will be documented as adverse events by the researcher at every visit, even if they are not necessarily related to the acupuncture intervention. The details of adverse events will be carefully recorded in the CRF by the corresponding research staff.

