## Background

Every woman has to undergo the menopausal transition as an inevitable stage of life. During this period, perimenopausal females usually complain of difficulties initiating and/or maintaining sleep with frequent nocturnal and early morning awakenings. Sleep disturbances are often multifactorial in origin and have a significant impact on the health-related life quality. The Study of Women’s Health across the Nation (SWAN) presents that the prevalence of sleep disturbance ascends with increasing age. Recent reviews revealed that the prevalence of insomnia in the perimenopausal women ranges from 39 to 47% [1], while it is approximately 35% in the general population [2].

In addition, with the increasing socioeconomic stress, there are more and more middle-aged women suffering from mood disorders, such as anxiety and depression, which have been noted to be closely related to sleep problems in postmenopausal women [3]. Difficulty in falling sleep has been shown to associate strongly with anxiety, with nonrestorative sleep also correlating strongly with depression, as well as results in anxiety, irritability, and nonrefresh sleep problems which in turn may manifest as depression [4]. Studies by Guidozzi et al. [5] also showed a significant correlation between depression and sleep-related disorders. According to these findings, sleep difficulties and emotional problems interact with and aggravate each other.

Currently, hypnotic medication such as benzodiazepine receptor agonists (estazolam in particular) has been recommended to be the first-choice medicine used routinely for chronic insomnia. Although estazolam is efficacious in the short-term management of insomnia, there is very limited evidence for long-term treatment efficacy [6]. Additionally, various adverse effects related to their use have been reported, including residual daytime sedation, cognitive impairment, and medication dependence [7–10]. Therefore, a large number of patients with insomnia are turning to complementary and alternative medicine such as acupuncture rather than hypnotic medication.

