## Discussion

This proposed study is a randomized, assessor–statistician-blinded, controlled clinical trial which is sponsored and financially supported by the National Nature Science Foundation of China. The purposes of this program are to evaluate the efficacy and safety of acupuncture for treating perimenopausal insomnia by assessing the sleep architecture, hormone level, and emotional-circuit neurological function, and to identify the effective mechanism of acupuncture regulating emotional center integration.

In the view that poor sleep quality during menopausal transition is closely related with mood disorder, the formula of acupuncture adopted in this trial will be based on syndrome differentiation from the liver. In recent years, there have been some published reports suggesting that treating insomnia according to syndrome differentiation from the liver is significantly effective [23, 24]. Some researchers investigated 3380 patients with insomnia in Shanghai and demonstrated that there are six basic types of insomnia: with hyperactivity of liver yang, stagnation of liver qi and blood, stagnation of liver qi invading the stomach, stagnation of liver qi invading the heart, fire derived from stagnation of liver qi, and wind derived from stagnation of liver qi [25]. On the basis of the syndrome differentiation from the liver, the previous study treated 2262 patients with sleep disturbance according to the therapeutic principle of soothing the liver, relieving depression, activating blood, and calming the mind; consequently it achieved a good curative effect [26]. Our pilot study also demonstrated that using acupuncture to treat perimenopausal insomnia from the liver is reliable and effective [14]. We therefore determined to design this study with the acupuncture intervention formula based on liver differentiation to provide evidence for the effects from clinical curative effect outcomes and the potential central mechanism.

Besides using the PSQI, MSMSMS, HAMD, and HAMA to assess the clinical curative effect, we choose fMRI technology to reveal the brain effective mechanism of acupuncture treatment for perimenopausal insomnia, as well as to provide clear, valid, and visual evidence.

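### The adverse-event recording rule contradicts the protocol's own list of expected events, gives no matching list for estazolam, and ties immediate reporting of serious events to a prior attribution judgement

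*Protocol article*

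**What the plan says.** Four statements in the Safety monitoring section of the protocol article matter here.

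- Recording rule: "All unexpected and unintended responses will be documented as adverse events by the researcher at every visit". The sentence continues with "even if they are not necessarily related to the acupuncture intervention".
- Expected events: "Possible adverse events due to acupuncture include needle fainting, needle sticking, local infections, subcutaneous hematoma, and so forth".
- Handling: "Any adverse events or reactions occur during the study process will be addressed properly and analyzed by the investigator". A later sentence sends the details of adverse events to the case report form.
- Serious events: "Serious adverse events associated with the trial should be reported to the principal investigator immediately".

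The section also repeats blood, urine, stool, liver, kidney and ECG tests in all participants after treatment, to look for side effects of either intervention.

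Elsewhere, the Background gives the harms reported for hypnotic medication, "including residual daytime sedation, cognitive impairment, and medication dependence", as a reason why patients turn to acupuncture. The Discussion states the aim of the programme as to "evaluate the efficacy and safety of acupuncture for treating perimenopausal insomnia". The Blinding section accepts that neither clinician nor patient can be masked.

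**The concern.** The sentence that says what becomes an adverse event sets two conditions joined by a conjunction: the response must be both unforeseen and not intended. A haematoma after needling or sedation the morning after a hypnotic is not intended, but it is foreseeable. On a literal reading it does not meet the rule, although the section elsewhere treats the needling reactions as adverse events.

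For acupuncture, a reader can resolve the conflict from the list. For estazolam there is nothing to resolve it with. The comparator effects that the protocol itself puts forward as a reason for the trial are the ones a literal reader is most likely to pass over.

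Safety is a stated purpose, and the abstract promises a safety assessment at every visit. If recording depends on how a member of staff reads the rule, and the reading is easier to settle in one arm than in the other, the comparison of harms may be distorted. An event that was not written down at the visit is hard to recover later. For serious events, the trigger for telling the principal investigator rests on an attribution judgement that may be made by someone who knows the arm.

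**Working it through.** No arithmetic applies. The protocol states no adverse-event rate, no safety power and no safety margin. The check sets the statements side by side.

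1. **Does the recording rule cover foreseeable harms?** Not by its own words, since it requires that the response be unforeseen. The added clause "even if they are not necessarily related to the acupuncture intervention" removes a condition on relatedness to acupuncture. It does not remove the condition on expectedness.

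2. **Do the neighbouring sentences cover them?** Partly. The list of needling reactions calls them adverse events outright. The handling sentence and the case report form sentence carry no filter on expectedness, cause or arm. Both, however, apply to events or reactions already recognised as such. The only sentence that says what is to be documented as an adverse event is the recording rule.

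3. **Is the position the same in both arms?**
   - *Acupuncture:* foreseeable reactions are listed in Safety monitoring, and the relatedness clause names this intervention.
   - *Estazolam:* no reactions are listed in Safety monitoring, and the relatedness clause does not name the drug. The known effects of hypnotics appear only in the Background.

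4. **Would other safety data pick up the Background effects?** The repeated laboratory tests and ECG are not designed to detect daytime sedation, impaired cognition or dependence. The Pittsburgh Sleep Quality Index has a daytime dysfunction component, but it is collected as efficacy and does not separate a drug effect from the insomnia. At follow-up, two weeks after treatment, patients document symptoms and adverse events themselves. No filter is stated there, but nothing says what counts.

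5. **Who makes the judgement?** The recorder is described only as the researcher or research staff. The article masks the outcome assessor and the statistician but not the clinician or the patient. A researcher who contacts control patients daily about their tablets, as Quality control provides, must know their arm.

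6. **What does the serious-event sentence restrict?** It restricts which events go to the principal investigator at once. It does not restrict what is recorded or analysed. On a natural reading, association with the trial has to be decided before the report is made.

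**The case against.** The strongest reply is that nothing is lost on this text. The recording rule says that certain responses will be documented; it does not say that only those will be. Needling reactions are called adverse events two sentences earlier, any event or reaction is to be analysed, and details go to the case report form. The relatedness clause widens recording, so an event caused by estazolam rather than acupuncture is still covered by it. Read literally, the rule would leave out expected events in both arms, so a difference between arms needs a further premise. The serious-event sentence sets urgency, not capture, and association with the trial need not mean causation. Quality control adds weekly monitoring, checks of source data and regular meetings that consider adverse events. The trial has one centre, and its investigators are trained and tested, including on the case report form. That form and the full protocol are not shown and may list sedation and similar complaints.

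Most of this stands, and it limits the point. A reader might infer that expected harms and unrelated serious events disappear from the safety comparison, or that a serious event judged unrelated is never seen by the principal investigator. The article supports neither inference, because no sentence excludes such events and the monitoring and meetings offer a later route.

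The reply does not remove the contradiction between the rule and the list. Nor does it supply for estazolam the list that settles the matter for acupuncture; that is the further premise a difference between arms needs. Training on the form helps only if the rule being taught is clear. With one centre, the inconsistency would lie between researchers rather than between hospitals.

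**Conclusion.** The point holds in a limited form. The article states a recording rule that conflicts with its own list of expected events, leaves the comparator's foreseeable effects to discretion, and makes immediate reporting of serious events depend on a prior attribution judgement. The consequence is a risk of inconsistent recording that may differ by arm, and of delay in escalation. It is not a demonstrated loss of data, and a biased safety result is possible rather than certain.

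The size cannot be put in numbers, because the documents give no event rates for either arm. The conclusion rests on two assumptions: that staff may read the rule literally, and that those who record or attribute events often know the arm. The Blinding and Quality control sections make the second likely but do not state it for every recorder. The point is modest in weight. It is worth acting on because the alternative wording costs little and the trial was still recruiting when the article was written.

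**What to change.** Reconcile the Safety monitoring section with three changes.

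1. Replace the recording rule with wording such as: any untoward occurrence in either group is recorded as an adverse event, whether or not it was expected and whether or not it is thought related to acupuncture or estazolam.
2. Ask about the effects named in the Background (daytime sedation, cognitive complaints, signs of dependence) at existing visits in both groups, with the same questions. The control group already has a weekly face-to-face interview when tablets are handed out. One acupuncture session a week could serve the other group, so that the frequency of asking matches.
3. State that all serious adverse events are reported immediately to the principal investigator regardless of suspected cause, and that causality is judged afterwards.

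This takes a few sentences and, if the case report form does not already have them, a few lines there. It needs no new visits or staff. The downside is that more events, including minor ones, will be reported in both arms.
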